##### Surface electromyography

2.4.2.2

The activities of the bilateral paraspinal muscles (at cervical, thoracic, and lumbar levels), quadriceps, semitendinosus, tibialis anterior, and lateral gastrocnemius will be measured by a 16-channel MyoMove-EOW sEMG system to systematically evaluate the overall muscle activation patterns of the spine and lower limbs during standing and walking states. Recordings will be obtained during both quiet standing and walking. Muscle recruitment will be assessed by analyzing the amplitude variation of the bioelectrical signals, with the root mean square value recorded for quantitative analysis.

##### Muscular temperature

2.4.2.3

The study will utilize the IRT to capture thermal images of the nape and back region of participants. Temperature changes in the bilateral paraspinal muscles (at cervical, thoracic, and lumbar levels) will be recorded.

##### Adverse events

2.4.2.4

During the treatment period, any newly emerged symptom will be documented as adverse events, including but not limited to aggravated pain, muscle spasms, dizziness, or headache. The physician will record in detail the severity, time of onset, duration, management measures, and course of each event. All AEs will be truthfully recorded on an AE form, capturing the time of occurrence, severity, duration, actions taken, and outcome. According to grading criteria for AEs, the clinical trial of this case should be stopped according to the judgment of the doctor and given compensation to those who suffer harm from trial participation when serious adverse events occur.

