The lower limbs, pelvis and spine are interconnected. Existing studies have widely reported that AIS patients typically exhibit biomechanical abnormalities in both the spine and lower limbs, such as asymmetric muscle activation, temperature differences in muscle activity, gait abnormalities and abnormal plantar pressure distribution, which further compromise spinal stability by disrupting the biomechanical balance between spine and lower limbs (6, 19–21). Understanding these biomechanical features is important for developing personalized rehabilitation strategies for AIS. However, the biomechanical changes of AIS patients are still controversial (22–24). The impact of TCMMT on biomechanics also has not been fully elucidated, and the quality of relevant studies still needs improvement (25, 26).

Thermography is a useful and noninvasive method of assessing muscular tension imbalance in the course of scoliosis (27). Combining with the plantar pressure, 3D gait analysis, and surface electromyography (sEMG) enables a comprehensive evaluation of the spine-limb biomechanical patterns during standing and walking in patients. Consequently, this study will employ the Cobb angle, the gold standard for scoliosis assessment (28), and integrate plantar pressure measurements, 3D gait analysis, surface electromyography (sEMG) and infrared thermography (IRT) to evaluate biomechanical changes. The study aims to elucidate the characteristics of biomechanical changes in AIS during standing and walking by comparing with healthy individuals at baseline, and provide evidence-based support for the efficacy and safety of combined TCMMT and Schroth method therapy by comparing baseline and post-treatment data of AIS.

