#### Randomization and blinding

2.2.7

Eligible patients will be randomly assigned to either the EG or the CG in a 1:1 ratio. The randomization sequence will be generated by a statistician not involved in outcome assessment using SPSS 27.0, and placed in opaque, sealed envelopes by a researcher not involved in trial intervention, assessment and data analysis. After an eligible patient is enrolled, the physician will obtain the allocation result by opening the corresponding envelope. Throughout the trial, the randomization sequence will remain inaccessible to other researchers. While blinding of the physicians and patients is not feasible, outcome assessors and the data statistician will remain blinded to group allocation.

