### Interventions

2.3

Patients in both groups will receive the Schroth method for 60 min, 5 times per week. In addition to the Schroth method, the EG will receive TCMMT for 20 min, 3 times per week. The total treatment duration for both groups will be 8 weeks. The HC will receive no treatment.

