### Quality control

2.6

The study protocol has been approved by the Second Affiliated Hospital of Tianjin University of Traditional Chinese Medicine Ethics Committee. To ensure the quality of the research and the safety of participants, all researchers involved in the study will undergo unified and standardized training. TCMMT interventions will be performed by attending physicians with over 5 years of experience. Training and instructional videos will be recorded by senior chief physicians from the Department of Rehabilitation, and training and assessment protocols will be developed. Only researchers who pass the assessment will be qualified to perform the interventions. The study will establish a clear testing process and develop standardized operational procedures to strictly control the quality of the observed indicators and ensure the safety of participants. Participants will be enrolled strictly in accordance with the diagnostic, inclusion, and exclusion criteria. If a participant fails to complete the treatment and observation period as required by the protocol, researchers will attempt to contact them to inquire about the reasons and complete the assessment items. All data will be objectively collected using a combination of paper records and electronic documentation. All issues encountered during the trial will be accurately recorded. Outcome assessors and statisticians will be strictly blinded.

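### An unblinded physician records adverse events, and the text ties recording to no occasion shared by the arms, so the safety comparison is open to unequal ascertainment

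*Protocol article*

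**What the plan says.** - **Aim.** The last paragraph of the Introduction says that the study will "provide evidence-based support for the efficacy and safety of combined TCMMT and Schroth method therapy". Adverse events are numbered 2.4.2.4, under the heading for secondary outcome measures.
- **Definition and window.** Section 2.4.2.4 opens: "During the treatment period, any newly emerged symptom will be documented as adverse events". Its list of examples then begins with a worsening of pain. The Methods part of the Abstract says instead that events are recorded for the whole of the trial.
- **Recorder.** "The physician will record in detail the severity, time of onset, duration, management measures, and course of each event" (section 2.4.2.4).
- **Blinding.** "While blinding of the physicians and patients is not feasible, outcome assessors and the data statistician will remain blinded to group allocation" (section 2.2.7).
- **Who gives the manual therapy.** "TCMMT interventions will be performed by attending physicians with over 5 years of experience" (section 2.6).
- **Contact schedule.** Section 2.3 gives each arm five hour-long Schroth sessions a week over 8 weeks. It describes the extra contact in one arm as follows: "In addition to the Schroth method, the EG will receive TCMMT for 20 min, 3 times per week".

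**The concern.** Whether a symptom counts as an adverse event, and how severe it is, is a matter of judgement. Most of the other outcomes are read from a radiograph or an instrument, and the plan protects them with blinded assessors. Adverse events depend most on judgement, yet they go to an unblinded role.

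Two mechanisms could make recording differ by arm:

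- **More opportunity.** The experimental group has extra hands-on sessions with a physician, in which a transient symptom is easily mentioned. This would raise its count.
- **Less inclination.** A physician who gives the manual therapy, or shares a department with those who do, may regard a symptom as part of treatment. Table 2 makes this concrete: in the technique for the convex side, soreness or pain is the cue to begin the plucking motion. Whether that soreness is an event has to be decided in one arm only. This would lower its count.

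The two pull in opposite directions, so neither a similar nor a different event rate could be read with confidence. The trial enrols children aged 8 to 15, and the article expects its results to inform clinical decisions. Unequal elicitation cannot be repaired once the data are collected.

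**Working it through.** **No plan figure to reproduce.** The article states no adverse event rate and no power for one. Its 30 patients per arm relates to the Cobb angle only.

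**Scheduled contact** (inputs from section 2.3)

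| Measure | Experimental | Control | Ratio |
|---|---|---|---|
| Schroth sessions | 5 × 8 = 40 | 5 × 8 = 40 | 1.0 |
| Manual therapy sessions | 3 × 8 = 24 | 0 | – |
| All sessions | 40 + 24 = 64 | 40 | 64/40 = 1.6 |
| Contact time | 40 × 60 min + 24 × 20 min = 2,880 min = 48 h | 40 × 60 min = 2,400 min = 40 h | 48/40 = 1.2 |
| Contact days, if Schroth is once a day and manual therapy falls on Schroth days (assumption) | 40 | 40 | 1.0 |

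The imbalance is thus 1.6, 1.2 or 1.0, depending on which measure of contact drives reporting. The article does not say which applies.

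**What unequal capture would do** (illustration; the capture probabilities are assumed)

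With the same true risk p in both arms, observed risk = p × capture probability. The observed risk ratio is then capture(experimental)/capture(control), and p cancels.

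- Equal capture: ratio 1.00.
- 90% against 70%: 0.90/0.70 = 1.29. With p = 20%, this is 18% against 14% observed.
- 90% against 50%: 0.90/0.50 = 1.80. With p = 20%, this is 18% against 10% observed.
- Reversed, 70% against 90%: 0.70/0.90 = 0.78.

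These figures show how sensitive the comparison is to capture. They do not estimate the bias in this trial.

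**Wording set side by side**

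- *Definition.* Section 2.4.2.4 limits events to symptoms that newly emerge, but its first example is pain that has got worse. Pain present at baseline that worsens is excluded by the rule and included by the example. The recorder has to choose.
- *Window.* Section 2.4.2.4 covers the treatment period; the Abstract covers the whole trial. A symptom that arises between the last session and the post-treatment assessment falls outside the first and inside the second.
- *Blinding.* Sections 2.2.7 and 2.6 promise blinded outcome assessors. Section 2.4.2.4 names the physician as recorder, and section 2.2.7 says that physicians cannot be blinded.

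**The case against.** Much can be said for the plan, and several stronger readings do not hold.

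- **The article is condensed.** The adverse event form, the grading criteria and the case report forms are not reproduced, and the SPIRIT schedule is a figure that cannot be seen. A reader might infer that no common reporting occasion exists. The documents do not support that. They show only that the text ties recording to none. This stands.
- **Recorder and therapist may differ.** A reader might infer that the recording physician is the one giving manual therapy. The article does not say so. Section 2.2.7 uses the same word for the person who opens the allocation envelope. The recorder is unblinded either way.
- **The control group is seen often.** It attends five times a week, and Table 1 describes hands-on work by a practitioner. A symptom lasting some days would meet a Schroth session in either arm. A reader might take the ratio of 1.6 to mean up to 60% more recorded events in the experimental group. That requires recording to be proportional to the number of sessions, which is extreme when contact time gives 1.2 and contact days may give 1.0.
- **Late symptoms.** A reader might infer from section 2.4.2.4 that symptoms after the last session go unrecorded. The Abstract says otherwise, so this is a conflict to reconcile, not a proven gap.
- **Safety has a modest place.** The Abstract's objective does not mention it, its list of secondary outcomes leaves adverse events out, and no specific between-arm comparison of them is described. The Introduction nevertheless states safety as an aim.
- **Lack of blinding is acknowledged.** The Discussion concedes possible bias and points to objective, quantitative measures. That does not help for dizziness, headache or pain.

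**Conclusion.** The concern holds as a risk, not as a certainty. Four stated facts support it: safety is an aim, an unblinded physician records and grades events, physicians deliver manual therapy to one arm only in 24 additional sessions, and the text links recording to no occasion shared by the arms. Together they leave between-arm comparisons of adverse events open to unequal ascertainment.

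A reader might go further and conclude that the rates will not be comparable. The documents do not support that. The size and direction of any bias cannot be derived from them, and with equal capture there would be none. The imbalance in scheduled contact is 1.6 by sessions and 1.2 by hours, and could be 1.0 by days.

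The inconsistencies in definition and window are in the text itself and rest on no assumption. The change is worth making before recruitment because it is cheap and cannot be made afterwards.

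**What to change.** 1. Put the same short fixed question list to both arms at a shared occasion, for example one Schroth session each week. Ask it again at the post-treatment visit, after all outcome measurements are complete. That is 8 + 1 = 9 occasions per patient.
2. Have it asked by Schroth staff who do not deliver manual therapy. Do not use the blinded outcome assessors: an answer such as soreness after manipulation could unblind the gait, electromyography and thermography assessments.
3. Define an event as any new or worsened symptom from randomisation to the post-treatment assessment, and use this wording in both the Abstract and section 2.4.2.4.
4. Base the between-arm comparison on these solicited reports. List events noted during manual therapy sessions separately.

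**Cost.** One short form and a few sentences in section 2.4.2.4, a few minutes per patient per week, and probably a higher reported event rate. Sample size, treatment and visits do not change. The Schroth staff may still know the allocation, so the remedy equalises the opportunity to report but does not guarantee blinded recording.

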### Data management and analysis

2.5

#### Data management

2.5.1

Data entry personnel and outcome assessors will receive standardized training in data management procedures. All participants’ information will be recorded in original case report forms. Two individuals will independently enter the data into Excel spreadsheets and cross-verify the entries for accuracy. In cases of improper data recording, the data manager will make necessary corrections. All paper documents related to the study will be securely archived, while electronic data will be stored on password-protected computers to ensure security of the data. All materials must be retained for at least 5 years after publication. If readers have questions regarding the published study findings, they may contact the corresponding author to request access to the original dataset. Personal information of participants will be kept confidential.

#### Data analysis

2.5.2

All statistical analysis will be performed by an independent statistician (blinded to group allocation) using SPSS 27.0. A *p*-value of <0.05 will be considered statistically significant. Continuous data will be summarized as mean ± standard deviation (M ± SD) or median with interquartile range. Categorical variables will be presented as frequencies or percentages.

This study will employ an intention-to-treat analysis, including all participants who were randomized and received at least one intervention session. Outcomes will be analyzed using two-sample *t*-tests or paired *t*-tests. If normality assumptions cannot be met, non-parametric tests will be used. For categorical variables, chi-square (χ^2^) tests will be performed. Inter-rater reliability will be assessed using the intraclass correlation coefficient. For case data with missing values, multiple imputation will be used to address the gaps.

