**Methods:**

This study is a randomized controlled trial. Sixty eligible AIS patients will be randomly allocated in a 1:1 ratio to either the experimental group (EG) or the control group. All patients will undergo Schroth method for 60 min, five times per week. The EG will additionally receive TCMMT for 20 min, three times per week. The treatment course will be 8 weeks. Furthermore, fifteen age-matched healthy volunteers will be included. The primary outcome measure is the Cobb angle assessed before and after treatment. Secondary outcome measures include plantar pressure and 3D gait parameters, surface electromyography and muscular temperature. Adverse events will be recorded throughout the trial. All patients randomly allocated in this study will be included in the intention-to-treat analysis.

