#### Sample size consideration

2.2.6

According to previous research (31), the Cobb angle was 10.87 ± 3.60°in EG after treatment, compared to 14.97 ± 5.01°in CG. Using the PASS 2021 software for calculation, with a sample size ratio set at 1:1, *α* = 0.05 (two-sided test), and a statistical power (1−*β*) of 0.90, while controlling the attrition rate within 15%, it is determined that 30 patients need to be recruited for each group. Therefore, this study will require the inclusion of a total of 60 patients. In addition, we will recruit 15 healthy individuals of the same age. They will compare with patients at baseline to evaluate biomechanical changes of AIS.

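### The Abstract and section 2.5.2 give the intention-to-treat label to two different sets; the narrower one can drop randomised patients who know their arm and never start

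*Protocol article*

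**What the plan says.** The protocol article defines its analysis set twice.

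- Abstract, Methods: "All patients randomly allocated in this study will be included in the intention-to-treat analysis". There is no condition on treatment received.
- Section 2.5.2, Data analysis: the analysis is again called intention-to-treat, but it is described as "including all participants who were randomized and received at least one intervention session".

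Three other places bear on the difference.

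- Section 2.2.7, Randomization and blinding: after enrolment "the physician will obtain the allocation result by opening the corresponding envelope". On blinding it says: "While blinding of the physicians and patients is not feasible, outcome assessors and the data statistician will remain blinded to group allocation".
- Section 2.5.2, missing data: "For case data with missing values, multiple imputation will be used to address the gaps".
- Section 2.6, Quality control: for participants who do not complete treatment and observation, "researchers will attempt to contact them to inquire about the reasons and complete the assessment items".

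**The concern.** The two sets differ as soon as one randomised patient attends no session. The section 2.5.2 set is then a modified intention-to-treat set carrying the intention-to-treat label.

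A modified set of this kind is usually defended on the ground that the reason for not starting cannot depend on the arm, because nobody knows the arm at that point. That defence is not available here. The envelope is opened before treatment, and neither the patient nor the physician is blinded. A family may decline once it knows what was drawn, and its reasons may differ by arm. Blinded reading of the radiographs protects the measurement of the Cobb angle, but not the question of whose Cobb angle is analysed.

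Two things are at stake: the comparability that randomisation provides, and a primary set fixed in advance. With both definitions on record, either could later be presented as the prespecified one after attendance by arm is known.

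**Working it through.** **1. The two definitions side by side**

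| Patient | Abstract | Section 2.5.2 |
|---|---|---|
| Randomised, completes treatment | in | in |
| Randomised, starts, then stops | in | in |
| Randomised, attends no session | in | out |

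The conflict is confined to the last row. The planned imputation does not repair it: under section 2.5.2 a never-starter is outside the set, so there is no record in the set to impute.

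**2. The plan's own sample size (section 2.2.6)**

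Inputs: "the Cobb angle was 10.87 ± 3.60°in EG after treatment, compared to 14.97 ± 5.01°in CG"; two-sided α 0.05; power 0.90; 1:1 allocation; 15% attrition.

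- Difference: 14.97 − 10.87 = 4.10°.
- Root-mean-square SD: √[(3.60² + 5.01²)/2] = √[(12.96 + 25.10)/2] = 4.36°.
- Two-sample t-test (noncentral t): 25 per group, with power 0.902 (equal variances) or 0.901 (Welch).
- Attrition: 25/0.85 = 29.4, rounded up to 30 per group.

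The stated 30 per group is reproduced, and the choice of analysis set does not change it.

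**3. Effect on power**

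The documents give no never-starter rate. Assume k = 0, 1, 2, 3 or 4 per arm. Section 2.5.2 would then analyse 60, 58, 56, 54 or 52 patients, with Welch power at the planning difference of 0.947, 0.939, 0.931, 0.923 or 0.912. Power stays above 0.90 throughout, so it is not the issue.

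**4. Possible shift in an arm mean (illustration; all selection assumptions are mine)**

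*Extreme selection.* Suppose 2 of 30 patients in one arm never start, and they are exactly those who would have had the two largest post-treatment angles. Removing the upper fraction p of a normal distribution lowers its mean by SD × φ(z)/(1 − p).

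- p = 2/30 = 0.0667; z ≈ 1.50; φ(z) ≈ 0.129; φ(z)/(1 − p) ≈ 0.139.
- Control arm, SD 4.36°: about 0.60°, which is 0.60/4.10 ≈ 15% of the planning difference.
- Control arm, its own SD of 5.01°: about 0.69°, or 17%.
- Experimental arm, its own SD of 3.60°: about 0.50°, or 12%.

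*Milder selection.* Suppose the k leavers would have been 4.1° worse on average than the rest of their arm. Dropping them lowers the arm mean by k × 4.1/30.

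- k = 1: 0.14°; k = 2: 0.27°; k = 3: 0.41°.

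*Direction.* A larger Cobb angle is worse. Dropping poor-outcome controls lowers the control mean, narrows the difference and understates the benefit. Dropping poor-outcome experimental patients lowers that mean and overstates it. With no never-starters the shift is zero.

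**The case against.** The case for treating this as minor is strong in several respects.

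- The sets differ only for patients who attend nothing at all. The 15% in section 2.2.6 is overall attrition and says nothing about failure to start. Patients who start and then stop are kept under both definitions. This stands.
- Both arms receive the same Schroth programme, so a control family still gets active treatment. The documents state no motive for refusing an arm. This also stands: arm-dependent non-starting is possible under the design but not shown.
- The 0.6° to 0.7° figure requires the leavers to be exactly the worst outcomes. It is an upper bound for two leavers and not an estimate.
- Imputation from observed data would largely fill in never-starters from patients of the same arm who did start. It would therefore come close to the restricted-set estimate and would not remove bias from selection on the unseen outcome. This stands, and it shapes the fix.
- A set of randomised patients with at least one session can be defended when it is named as such. What fails here is the name and the conflict with the Abstract.

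The objection does not remove the conflict. This is not detail held over for an analysis plan: the article states the rule twice, with different content. A reader might go further and infer that the section 2.5.2 rule will bias the primary result, or that it favours the manual-therapy arm. The documents support neither inference, since they give no rate of non-starting, no pattern by arm and no direction.

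**Conclusion.** The point holds as an inconsistency in the current text about who is analysed, with an open-allocation route by which the narrower definition could exclude patients selectively. The size and direction of any resulting bias cannot be derived from the documents. Under assumed losses of 2 of 30 in the control arm, the benefit would be understated by at most about 0.6° to 0.7°, and by about 0.3° under milder selection. Losses in the experimental arm would work in the opposite direction. If every randomised patient attends one session, nothing changes. The planned size and the power are not in question. Severity: should-fix, before attendance and outcome data are examined by arm.

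**What to change.** 1. In section 2.5.2, define the primary analysis set as all randomised patients, analysed in the arm to which they were allocated, whatever number of sessions they received. This agrees with the Abstract.
2. State that the section 2.6 effort to contact patients and complete assessments also applies to those who never start, so that their post-treatment Cobb angle is observed where possible.
3. Use the multiple imputation already planned for Cobb angles still missing, and acknowledge that it assumes missingness is explained by observed data.
4. If the set requiring at least one session is kept, call it modified intention-to-treat and use it only as a sensitivity analysis.

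The textual cost is a sentence or two in section 2.5.2 and a clause in section 2.6. The planned 60 patients are unchanged. The only practical cost is the effort to obtain follow-up assessments from any never-starters, which section 2.6 already largely foresees.

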### Study design and settings

2.1

This study is a prospective randomized controlled trial. This study compares the biomechanical patterns between AIS patients and healthy individuals during standing and walking using technologies such as plantar pressure measurements, 3D gait analysis, sEMG, and IRT, and observes changes in patients before and after treatment. The research will be conducted at the Rehabilitation Medicine Department of the Second Affiliated Hospital of Tianjin University of Traditional Chinese Medicine. A total of 60 patients will be enrolled, along with 15 healthy individuals of similar age. Patients in the control group (CG) will perform the Schroth method for 60 min, five times per week. The experimental group (EG) will receive 20-min TCMMT three times per week in addition to the Schroth method. The total treatment duration for both groups is 8 weeks. The healthy control (HC) will receive no intervention. All patients will be assessed for Cobb angle, 3D gait parameters, sEMG and IRT before and after treatment. The healthy individuals will receive all assessments except the Cobb angle measurement only upon enrollment. The SPIRIT schedule of participant timeline is shown in Figure 1 and the flow chart of the trial procedure is presented in Figure 2.

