#### Inclusion criteria

2.2.2

Diagnostic criteria for idiopathic scoliosis (1).Ages 8 to 15 years, skeletal immaturity (defined as a Risser grade ≤2) (29, 30).Major curve Cobb angle 10° ~ 40°.No obvious deformities in the lower limbs and feet.Can understand and follow instructions to walk independently.Can understand and voluntarily participate in, and sign the informed consent form.

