#### Primary outcome measure

2.4.1

All AIS patients will require the standing frontal radiograph. The Cobb angles will be measured by two blinded and independent radiologists before and after the treatment.

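### The primary Cobb comparison is planned without adjustment for baseline Cobb and without naming the analysed variable; ANCOVA would gain precision at no cost

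*Protocol article*

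**What the plan says.** The Protocol article, Data analysis (2.5.2), gives one rule for all continuous outcomes: "Outcomes will be analyzed using two-sample *t*-tests or paired *t*-tests". It adds: "If normality assumptions cannot be met, non-parametric tests will be used". It sets out no separate method for the primary outcome and names no covariate, regression or mixed model. The same section requires multiple imputation for missing values.

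Baseline Cobb will be available. Under Primary outcome measure (2.4.1), "The Cobb angles will be measured by two blinded and independent radiologists before and after the treatment". Study design and settings (2.1) says the same of all patients: "All patients will be assessed for Cobb angle, 3D gait parameters, sEMG and IRT before and after treatment". The Inclusion criteria admit "Major curve Cobb angle 10° ~ 40" degrees. Randomization and blinding (2.2.7) says "Eligible patients will be randomly assigned to either the EG or the CG in a 1:1 ratio" and mentions no stratification or other balancing on curve size.

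Sample size consideration (2.2.6) is built on post-treatment angles alone: "the Cobb angle was 10.87 ± 3.60°in EG after treatment, compared to 14.97 ± 5.01°in CG".

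**The concern.** The angle before treatment is the obvious predictor of the same angle eight weeks later. A two-sample t-test on post-treatment angles ignores it. Differences between patients that were present at entry then stay in the error term, and any chance difference between the arms at baseline carries into the estimated treatment effect in proportion to the pre-post correlation. With 60 patients and no stated balancing on curve size, that exposure is not negligible.

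The wording also leaves the analysed variable open. A two-sample test could be run on post-treatment values or on changes, and these are different analyses with different precision. A paired t-test compares before with after within one arm and does not compare the arms. In addition, the choice between t-test and non-parametric test depends on a normality check on the trial data. A single pre-named primary analysis would close all of these choices.

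**Working it through.** **Inputs from the Protocol article.** Post-treatment means 10.87° and 14.97°, SDs 3.60° and 5.01°, two-sided alpha 0.05, power 0.90, attrition 15%, 30 per group (all from 2.2.6).

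**Inputs not in the document, so assumed.** The pre-post correlation r (0.3 to 0.8) and the SD of Cobb in this trial. For the SD I use the pooled planning value, then 6°, 7.07° and 8.66°. The last is the SD of a uniform spread over 10°-40°: 30/√12 = 8.66. Each SD is taken to apply at baseline and after treatment.

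**1. The plan's own figure.** Difference = 14.97 − 10.87 = 4.10°. Pooled SD = √((3.60² + 5.01²)/2) = 4.36°. Standardised difference = 4.10/4.36 = 0.94. A two-sample t-test (noncentral t) needs 25 per arm, with power 0.902. Then 25/0.85 = 29.4, rounded up to 30. The stated 30 per group is reproduced, as an unadjusted comparison of post-treatment values.

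**2. Effect of adjusting for baseline.** The ANCOVA residual SD is SD × √(1 − r²), with one degree of freedom fewer. The error variance is multiplied by 1 − r²: 0.91, 0.75, 0.51 and 0.36 at r = 0.3, 0.5, 0.7 and 0.8. Power for 4.1° with 25 evaluable per arm:

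| SD | Unadjusted | ANCOVA r=0.3 | r=0.5 | r=0.7 | r=0.8 |
|---|---|---|---|---|---|
| 4.36° (planning) | 0.90 | 0.93 | 0.96 | 0.995 | >0.999 |
| 6° | 0.66 | 0.70 | 0.78 | 0.91 | 0.98 |
| 7.07° | 0.52 | 0.56 | 0.64 | 0.80 | 0.92 |
| 8.66° | 0.37 | 0.40 | 0.47 | 0.63 | 0.78 |

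**3. If the t-test were on changes.** The SD of the change is SD × √(2(1 − r)). At SD 4.36° the power is 0.79, 0.90 and 0.988 at r = 0.3, 0.5 and 0.7. At SD 7.07° and r = 0.8 it is 0.89. ANCOVA has higher power at each of these points. At r = 0.3 the change score does worse than ignoring baseline altogether (0.79 against 0.90).

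**4. Chance baseline imbalance, 30 per arm, no stratification.** SE of the baseline difference = SD × √(2/30).

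| SD | SE | P(imbalance > 2° in either direction) |
|---|---|---|
| 4.36° | 1.13° | 0.08 |
| 6° | 1.55° | 0.20 |
| 7.07° | 1.83° | 0.27 |
| 8.66° | 2.24° | 0.37 |

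With equal SDs before and after, a 2° imbalance shifts the unadjusted estimate by about r × 2°. At r = 0.8 that is 1.6°, or 1.6/4.1 = 39% of the planned effect.

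**The case against.** The strongest reply is that the planned test and the sample size agree. At the protocol's own SD the unadjusted t-test has power 0.902, as stated. It is valid under 1:1 randomisation, and its standard error already allows for chance imbalance. All of this stands.

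A reader might infer more than the document supports:

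- **That most of the power is lost.** The fall to 0.52 comes from replacing the planning SD of 4.36° with an assumed 7.07°. That is a doubt about the planning SD, not a result of the choice of test. The recovery to 0.92 also needs r = 0.8.
- **That the eligibility limits make non-normality likely.** The 10° and 40° limits apply at entry and do not bound the post-treatment angle. No figure in the document shows that normality will fail.
- **That the fallback gives no estimate in degrees.** The text says only that the tests will be non-parametric. A Mann-Whitney test can be reported with a Hodges-Lehmann shift and its interval, in degrees.
- **That baseline is certainly ignored.** A two-sample test on changes would use it, and the text does not exclude this. The sample size points to post-treatment values but does not settle the matter.

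It can also be said that an article condenses a fuller plan, where covariates are often specified. But this article does state the method for its outcomes, so the point concerns a stated choice and not a missing detail.

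**Conclusion.** The point holds as a loss of precision that costs nothing to avoid, together with an unspecified analysis variable. It is not an invalid test, an inflated type I error or a wrong sample size.

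At the planning SD of 4.36° the gain from ANCOVA is from 0.90 to between 0.93 and 0.995 for r from 0.3 to 0.7. The gain matters more if the trial's angles spread more widely than planned, which the eligibility range permits but the document does not show. The chance of a baseline imbalance above 2° is about 8% at the planning SD and 20-37% at SDs of 6-8.66°. Every figure beyond the 0.902 rests on assumed r or on an SD carried over to this trial. The direction does not: ANCOVA had higher power than both the unadjusted and the change-score test at every combination computed.

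**What to change.** In Data analysis (2.5.2), name as the single primary analysis a linear model (ANCOVA) of post-treatment major-curve Cobb angle on arm and baseline Cobb angle. Report the EG minus CG difference in degrees with its 95% confidence interval. Fit the model in each imputed dataset and pool the results. If residuals are clearly non-normal, keep the model and use robust or bootstrap standard errors, without switching tests on a normality check. Apply the same model to the secondary measures taken before and after treatment. Any paired tests should be labelled as within-arm description.

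The cost is one paragraph. The data are already to be collected, the named software (SPSS 27.0) fits the model, and 60 patients remain enough under the protocol's own assumptions. The change should be made before any outcome data are seen, so that the adjustment cannot look like a response to an observed imbalance.
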